#### Secondary endpoints

Every secondary endpoint will be determined for patients included in the recommended scheme administration (expansion phase):

PFS according to RECIST v1.1 and iRECIST, or death from any cause, whichever occurs first. It will be evaluated at 12 months. Additionally, the median will also be displayed.Long-term safety of the SBRT, atezolizumab, and tiragolumab antibody combination will be evaluated with acute and late adverse events (AAEs) according to CTCAE 5.0.Acute adverse events are adverse events occurring within the first sixth months, and late adverse events are adverse events occurring after the first six months.Overall survival (OS) is defined as the time from inclusion to death from any cause.Overall response rate (ORR) and non-progression rate (NPR) are evaluated from the first two evaluation scanner images carried out at 9 and 18 weeks after time from inclusion (CT-scan forecast before the 3rd and 6th cure) as determined by the investigator according to RECIST v1.1 and iRECIST. Overall response is defined by a partial or complete response. Non-progression is defined by a partial or complete response and a stable disease.Duration of response (DOR) is defined as the time from documentation of a disease complete or partial response to disease progression, defined according to RECIST v1.1 and iRECIST. Non-progression duration (NPD) is defined as the time from documentation of a complete response, partial response, or stable disease to a disease progression, as defined according to RECIST v1.1 and iRECIST.Abscopal effect is evaluated following non-irradiated metastasis volume(s) from scanner images.

### Exploratory endpoint

Immunohistology for PDL1 (Sp142 and 22C3), TIGIT, CD155, and CD112Immunohistology before treatment and after 2 months of therapy to study immune infiltrates (PDL1, CD112, CD155, CD8, CD19, DC-Lamp, TCF1, CD163) using multiplex immune histology and spatial transcriptomic profiling for a sample of good responders or stable and poor responders (progressing straight away)Study of peripheral immune response upon multiparametric cytometry and multiplex cytokine testing at baseline and following treatmentStudy of a specific peripheral immune response against two shared antigens (telomerase and NY-ESO1) on isolated peripheral blood mononuclear cells (PMBC). Telomerase and NY-ESO1-specific T-cell responses will be assessed by a standardized IFN-γ ELISPOT assay.Neopeptide detection upon exome sequencingStudy of the impact of the total volume receiving the prescribed dose on specific tumor immune response

### Study population and eligibility criteria

Patients will be included in different cohorts, depending on the type of histologically proven metastatic cancer:

Cohort 1 (phase I and expansion cohorts phase) : non-small cell lung cancer without oncogenic addiction (EGFR/ALK/ROS/BRAF) that progresses after platinum-based chemotherapy and immunotherapy given as sequential or concomitant therapyCohort 2 (expansion cohorts phase only) : bladder cancer that progresses after platinum-based therapy with or without maintenance with anti-PD-1/PD-L1Cohort 3 (expansion cohorts phase only): renal cell carcinoma in second-line therapy that progresses after a first-line administered according to the guidelines for the standard of care in renal cancer. First-line therapy could include an antiangiogenic agent, a tyrosine kinase inhibitor, alone or associated with immunotherapy (anti-PD-L1, anti-CTLA4)Cohort 4 (expansion cohorts phase only): head and neck carcinoma at the first line of locoregional or metastatic recurrence. The patient should not be eligible for surgery.

Study inclusion and exclusion criteria are detailed in Tables 1 and 2.

**Table 1 Tab1:** Study inclusion criteria.

*Study inclusion criteria*
1. Male or female that must have signed a written informed consent prior to any study specific procedures
2. Aged ≥ 18 years at randomization
3. Performance status of 0 or 1 according to the WHO Easter Cooperative Oncology Group (ECOG)
4. Minimum 3 measureable lesions, with at least one lesion which cannot be irradiated for testing the abscopal effect and at least 2 irradiable lesions. Those lesions must be uni-dimensionally ≥ 10 mm considered as measurable according to RECIST v1.1.
5. Life expectancy > 6 months
6. At least one non-irradiated tumor site that can be biopsied for research purpose
7. Participant must have following advanced disease and must not be a candidate for other approved therapeutic regimen known to provide significant clinical benefit based on investigator judgement : - Cohort 1 (phase I and expansion cohorts phase) : non-small cell lung cancer without oncogenic addiction (EGFR/ALK/ROS/BRAF) which progress after platin based chemotherapy and immunotherapy given as sequential or concomitant therapy - Cohort 2 (expansion cohorts phase only) : bladder cancer which progress after platin based therapy with or without maintenance with anti PD-1/PD-L1 - Cohort 3 (expansion cohorts phase only) : renal cell carcinoma in second-line therapy which progress after a first line administered according to the guidelines for the standard of care in renal cancer. First line therapy could include antiangiogenic agent, tyrosine kinase inhibitor, alone or associated with immunotherapy (anti-PD-L1, anti-CTLA4) - Cohort 4 (expansion cohorts phase only) : head and neck carcinoma at the first line locoregional or metastatic recurrence. Patient should not be eligible to surgery.
8. Participants who received prior anti-PD-1/L1 therapy must fulfill the following requirements - Have achieved a complete response, partial response or stable disease and subsequently had disease progression while still on anti-PD-1/L1 therapy - Have received at least two doses of an approved anti-PD-1/L1 therapy (by any regulatory authority) - Have demonstrated disease progression as defined by RECIST v1.1
9. Adequate hematological, renal, metabolic and hepatic functions: - Hemoglobin ≥ 9 g/dl (participants may have received prior red blood cell [RBC] transfusion, if clinically indicated (but should be performed with 1 week delay between transfusion and validation of eligibility criteria); absolute neutrophil count (ANC) ≥ 1.5 G/l, platelet count ≥ 100 G/l, white blood cell count ≥ 2.5 G/l (or within local laboratory normal limits) and lymphocyte count ≥ 0.75 G/l -. Alkaline phosphatase (AP), alanine aminotransferase (ALT) and aspartate aminotransferase (ASP) ≤ 2.5 x upper limit of normality (ULN) (≤ 5 x ULN in case of extensive skeletal involvement for AP exclusively and ≤ 5 x ULN in case of liver metastasis for AST and ALT). - Total bilirubin ≤ 1.5 x ULN, (3 x ULN for gilbert disease) - Albumin ≥ 25 g/l. - Serum creatinine ≤ 1.5 x ULN or calculated creatinine clearance (CrCl) ≥ 30 ml/min (according to Cockcroft and Gault formula). - INR ≤ 1.5 x ULN - aPTT ≤ 1.5 X ULN - Serum calcium within normal laboratory ranges,
10. No prior or concurrent malignant disease if more recent than 3 years
11. At least three weeks since last chemotherapy, immunotherapy or any other pharmacological treatment and/or radiotherapy
12. At least 2 mesurable lesions should be able to receveid 3 X 8 Gy by SBRT according to the dose constraints to organs at risk (OAR) imposed by the protocol
13. In case of lesion previously treated by radiotherapy, the constraints on the organs at risk must be respected after having summed up the treatment plans

**Table 2 Tab2:** Study exclusion criteria.

*Study exclusion criteria*
1. Evidence of symptomatic central nervous system (CNS) or leptomeningeal metastases
2. Women who are pregnant or breast feeding
3. Participation in a study involving a medical or therapeutic intervention in the last 30 days
4. Previous enrolment in the present study
5. Participant unable to follow and comply with the study procedures because of any geographical, familial, social or psychological reasons
6. Known hypersensitivity to any involved study drug or of its formulation components
7. History of severe allergic anaphylactic reactions to chimeric, human or humanized antibodies, or fusion proteins
8. Treatment with systemic immunosuppressive medications including, but not limited to, cyclophosphamide, azathioprine, methotrexate, thalidomide, and anti-TNF agents within 2 weeks prior to inclusion. Systemic corticosteroids is not allowed but at physiologic doses meaning less than 10 mg/day of prednisone or its equivalent. The use of inhaled corticosteroids and mineral corticoids is allowed
9. Major surgical procedure, open biopsy or significant traumatic injury within 28 days before inclusion
10. Any of the following cardiac criteria: - Congestive heart failure ≥ New York Heart Association (NYHA) class 2, - Unstable angina (angina symptoms at rest), new-onset angina (begun within the last 3 months), - Myocardial infarction less than 6 months before inclusion - Uncontrolled cardiac arrhythmias, - Known left ventricular ejection fraction (LVEF) < 50%
11. Individuals deprived of liberty or placed under legal guardianship, curatorship or judicial protection
12. Prior organ transplantation, including allogeneic stem cell transplantation
13. Known clinically significant liver disease, including, alcoholic, or other hepatitis, cirrhosis, fatty liver and inherited liver disease, active viral with positive viral DNA detection
14. History of intra-abdominal inflammatory process within the last 12 months such as, but not limited to, diverticulitis, peptic ulcer disease or colitis
15. History of autoimmune disease including, but not limited to systemic lupus erythematosus (SLE), Sjögren’s syndrome, glomerulonephritis, multiple sclerosis, rheumatoid arthritis, vasculitis, systemic immune activation, inflammatory bowel disease, vascular thrombosis associated with antiphospholipid syndrome, Wegener’s granulomatosis, Guillain-Barré syndrome, Bell’s palsy - Participants with a history of autoimmune-related hypothyroidism on a stable dose of thyroid replacement hormone are eligible - Participants with controlled Type I diabetes mellitus on a stable insulin regimen are eligible - Participants with eczema, psoriasis, lichen simplex chronicus, or vitiligo with only dermatologic manifestations < 10% of the skin (e.g., participants with psoriatic arthritis would be excluded) are eligible
16. History of idiopathic pulmonary fibrosis, organizing pneumonia (e.g. bronchiolitis obliterans), drug-induced pneumonitis, idiopathic pneumonitis, or evidence of active pneumonitis on screening chest CT scan. History of radiation pneumonitis in the radiation field (fibrosis) is permitted
17. Poorly controlled Type II diabetes mellitus defined as a screening fasting plasma glucose ≥ 160 mg/dL (or 8.8 mmol/L)
18. Severe infections within 2 weeks prior to inclusion, including but not limited to SARS-Cov-2 infection, hospitalization for complications of infection, bacteremia, or severe pneumonia
19. Received therapeutic oral or IV antibiotics within 2 weeks prior to inclusion. Participants receiving prophylactic antibiotics (e.g., for prevention of a urinary tract infection or chronic obstructive pulmonary disease) are eligible
20. Any contraindication to tumor biopsy
21. Participant with spinal cord compression not definitively treated with surgery and/or radiation or previously diagnosed and treated spinal cord compression without evidence that disease has been clinically stable for > 2 weeks prior to inclusion
22. Administration of a live, attenuated vaccine within 4 weeks before the start of study medication or anticipation that such a live attenuated vaccine will be required during the study. Influenza vaccination is allowed during influenza season only (approximatively October to March)
23. Patient with a known history of Human Immunodeficiency Virus (HIV) (HIV1/2 antibodies) or known acquired immunodeficiency syndrome (AIDS),
24. Patients with EBV infection (Positive EBV viral capsid antigen IgM test at screening)
25. Active tuberculosis
26. Concomitant use of prohibited concomitant therapy (cf paragraph 6.5.2.2) or anticipation that such concomitant medication/therapies will be required during the study
27. For NSCLC indication, patients with lymphoepithelioma-like carcinoma are excluded
28. Female patients who are pregnant or breastfeeding or male or female patients of reproductive potential who are not willing to employ effective birth control from screening to 5 months after the last dose of atezolizumab and/or tiragolumab and 6 months following the last dose of radiotherapy

### Investigational combination products

Atezolizumab is a humanized IgG1 Mab that targets PD-L1 and inhibits the interaction between PD-L1 and its receptors, PD-1 and B7-1 (also known as CD80), both of which function as inhibitory receptors expressed on T cells. Therapeutic blockade of PD-L1 binding by atezolizumab has been shown to enhance the magnitude and quality of tumor-specific T-cell responses. Atezolizumab has minimal binding to Fc receptors, thus eliminating detectable Fc-effector function and the associated antibody-mediated clearance of activated effector T cells.

Tiragolumab (formerly MTIG7192A) is a fully human IgG1/κ Mab derived in open monoclonal technology rats that binds to TIGIT and prevents its interaction with the poliovirus receptor. The recombinant antibody is produced in Chinese hamster ovary (CHO) cells and consists of two heavy chains (456 amino acid residues each) and two light chains (220 amino acid residues each). There are two N-linked glycosylation sites (Asn306) in the Fc domain. The predicted molecular weight of tiragolumab is 148,409 Da (peptide chains only, without heavy chain C-terminal lysine residue). By binding to TIGIT, tiragolumab blocks its interaction with a protein called CD155 (poliovirus receptor) that can suppress the body’s immune response. Therapeutic blockade of TIGIT by means of tiragolumab represents an attractive strategy for cancer therapy and is expected to enhance the magnitude and quality of the tumor-specific T-cell responses, which may result in improved meaningful anti-tumor activity when tiragolumab is used as a single agent or in combination with other ICIs.

### Investigational procedure

Each lesion will be treated with SBRT using 3 fractions of 8 Gy prescribed on the PTV (Planned Tumor Volume), with one fraction delivered every day, ideally Monday, Wednesday, and Friday, so the treatment period will therefore be five days. For technical reasons (breakdown, maintenance, etc.), two fractions will be delivered over two successive days, with a minimum delay of 24 hours between two fractions. A total treatment period of 5 days will be accepted.

Treatment must be delivered by a regular LINAC (Linear Accelerator) or MRI (Magnetic resonance Imaging) machine using the SBRT technique to all lesions and isocenters. Daily IGRT (Image-Guided Radiation Therapy) is required. If it’s possible, we encourage avoiding the VMAT (Volumetric Modulated Arc Therapy) technique to decrease the risk of lymphopenia, which may be associated with anti-tumoral immunity reduction. For this SBRT prescription condition, at least 95% of PTV will have to receive 100% of the prescribed dose (24 Gy).

Patients included in this study will present at least three lesions. In order to guide which lesions to irradiate, the following principles should be used:

To irradiate at least two measurable lesionsTo let at least one measurable non-irradiated lesion to evaluate the abscopal effect. Of note, this non-irradiated lesion can be the one biopsied.To try to irradiate the majority of the lesions, however, it is mandatory to respect the constraints on OARs (organs at risk).

Dose constraints for OARs are defined in Table 3 according to Timmerman et al [21].

**Table 3 Tab3:** Dose contraints to OARs

**OARs**	**Dmax (Gy)**	**Volume**
Optic nerve	19.5	V15 < 0.2 cc
Cochlea	20	
Brainstem	23	V18 < 1 cc
Spinal Cord	22	V18 < 0.25 cc; V11.1 < 1.2 cc
Cauda equina	24	V21.9 < 5 cc
Sacral plexus	24	V22.5 < 3 cc
Esophagus	27	V21 < 5 cc
Ipsilateral brachial plexus	24	V22.5 < 3 cc
Heart/pericardium	30	V24 < 15 cc
Great vessels	45	V39 < 10 cc
Trachea and Ipsilateral bronchus	30	V15 < 4 cc
Skin	24	V22.5 < 10 cc
Stomach	24	V21 < 10 cc
Duodenum	24	V15 < 5 cc
Jejunum / ileum	27	V16.2 < 5 cc
Colon	30	V20.4 < 20 cc
Kidneys (right and left) Rectum		V14 < 200 cc, V15 < 33%
Rectum		V20.4 < 20 cc
Bladder	30	V15 < 15 cc
Penil Bulb	30	V21.9 < 3 cc
Femoral Heads (right and left)	42	V21.9 < 10 cc
Renal Hilum/vascular trunk		V18.6 < 2/3 volume
Normal Lung (homolateral lung – ITV) (if one lung lesion)		V20 < 10%
Normal Lung (bilateral lung – ITV) (if several lung lesions)		V19 < 6.5%
Normal Liver (Liver – ITV)		V15 < 700 cc

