### Expected treatment-related adverse events

The possible toxicity of a combination of radiotherapy and immunotherapy mainly depends on the location of the irradiation and may involve hepatitis for liver irradiation or autoimmune pneumonitis for lung irradiation. However, such side effects are transitory and manageable. In a phase I study, administration of SBRT before immunotherapy appeared safe with acceptable toxicity. The most common treatment-related adverse events were general disorders and administration site abnormalities. Other frequent mild adverse events (> 20%) included gastrointestinal disorders, metabolism and nutrition disorders, musculoskeletal and connective tissue disorders, and respiratory, thoracic, and mediastinal disorders [19].

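### Table 3 gives the kidneys two limits 1 Gy apart that imply very different tolerances, so one looks redundant or mis-stated; the liver entry of similar size should be checked with it

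*Protocol article*

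**What the plan says.** The Investigational procedure section of the protocol article states that "Dose constraints for OARs are defined in Table 3", with a cited publication as the source. The table's volume limits all take the form of an upper bound: the volume receiving at least a given dose must stay below a figure.

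- **Kidneys:** "V14 < 200 cc, V15 < 33" (the last figure is a percentage), with no maximum dose. The row is labelled for the right and left kidneys but does not say whether the limits apply to each kidney or to both together.
- **Normal liver:** V15 < 700 cc, with no maximum dose and no percentage limit.
- **All other absolute volumes in the table:** between 0.2 and 20 cc.

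The limits are binding. Centres should try to irradiate most lesions, but "it is mandatory to respect the constraints on OARs (organs at risk"). Inclusion criterion 12 in Table 1 also depends on them: at least two measurable lesions must be able to receive 3 x 8 Gy "according to the dose constraints to organs at risk (OAR) imposed by the protocol". The Study design section makes phase I monocentric and the expansion phase multicentric.

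**The concern.** Two limits on one organ at 14 and 15 Gy should describe roughly the same tolerance, because the volume receiving 14 Gy usually differs little from the volume receiving 15 Gy. These two do not. The percentage limit allows about a third of the organ, whereas the absolute limit allows half or more of it at any kidney volume that seems reasonable to assume. A limit that adds nothing to the one printed beside it suggests that a figure, its direction or the organ it refers to was set down wrongly.

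The table decides which lesions may be irradiated and, through criterion 12, which patients may enter. Several centres will plan to these constraints in the expansion phase. If one centre takes 200 cc or 700 cc literally and another takes it as a volume to be spared, they will apply different rules under one protocol. The liver matters here because it has no second limit, and the section on expected adverse events says that toxicity "may involve hepatitis for liver irradiation or autoimmune pneumonitis for lung irradiation".

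**Working it through.** **Inputs from the document.** Kidney V14 < 200 cc and V15 < 33%; liver V15 < 700 cc (Table 3).

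**Assumed inputs, not in the document.** Both kidneys together 250 to 400 cc; one kidney 125 to 200 cc; normal liver 1,000 to 2,000 cc. T is the organ volume.

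**1. Where the kidney limits agree.** 200 = 0.33 x T gives T = 200 / 0.33 = 606 cc, well above the assumed range.

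**2. Both kidneys combined.**

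| T (cc) | 200 cc as % of T | 33% of T (cc) | Gap, 200 - 0.33T (cc) |
|---|---|---|---|
| 250 | 80% | 82.5 | 117.5 |
| 300 | 67% | 99 | 101 |
| 350 | 57% | 115.5 | 84.5 |
| 400 | 50% | 132 | 68 |

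V14 equals V15 plus the volume lying between 14 and 15 Gy. A plan that meets the percentage limit can therefore breach the absolute one only if that 1 Gy band holds at least the gap in the last column, about 68 to 118 cc of kidney. The absolute limit is close to redundant.

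**3. Per kidney.** 200 / 125 = 160% and 200 / 200 = 100%. The absolute limit is the whole organ or more, so it restricts nothing. The percentage limit is 0.33 x 125 = 41 cc to 0.33 x 200 = 66 cc.

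**4. Mixed reading.** Suppose 33% applies to each kidney and 200 cc to the pair. If each kidney is below 33%, the pair is below 33% of its combined volume, so the comparison in step 2 still holds.

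**5. One possible explanation: 200 cc is a volume to be kept below the dose.** The irradiated part would then be T - 200:

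- 250 cc: 50 / 250 = 20%
- 300 cc: 100 / 300 = 33%
- 350 cc: 150 / 350 = 43%
- 400 cc: 200 / 400 = 50%

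It equals 33% exactly at T = 200 / 0.67 = 298.5 cc. This fits the percentage limit near 300 cc combined and departs from it elsewhere.

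**6. Liver, the two readings side by side.**

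| T (cc) | As printed, 700 / T | If 700 cc is spared, (T - 700) / T |
|---|---|---|
| 1,000 | 70% | 30% |
| 1,400 | 50% | 50% |
| 2,000 | 35% | 65% |

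They coincide when T - 700 = 700, that is at 1,400 cc. Below that volume the printed limit is the more permissive; above it the printed limit is the stricter.

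**The case against.** The strongest reply is that nothing here is contradictory. Both kidney entries are upper bounds, one plan can satisfy both, and the stricter governs. The percentage limit still applies, so no kidney harm follows from the redundancy. This stands: a reader might infer that the two limits are incompatible, and they are not. The mismatch also rests on organ volumes that the article does not give.

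Second, a reader might infer that the 200 cc figure was inverted. Its agreement with 33% is confined to about 300 cc combined. Per kidney, sparing 200 cc out of 125 to 200 cc is impossible or requires the whole organ. The article nowhere mentions a spared volume, and only the cited source could settle the matter. Inversion therefore remains a possibility to check.

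Third, it is tempting to say that the liver limit points the wrong way and lets too much liver be irradiated. The article does not support that. The liver has one limit, nothing contradicts it, and for livers above 1,400 cc the spared-volume reading would allow more irradiation than the printed one. What remains is its unusual size, shared only with the kidney figure. The lack of a maximum dose is weaker evidence, since the rectum, renal hilum and lung rows have none either.

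Fourth, a reader might infer that centres would count dose-limiting toxicities differently and so distort the choice of scheme. Phase I runs at one centre, so differences between centres cannot affect that decision. At most they could touch the later safety review of the expansion cohorts by the monitoring committee. The adverse-event section also names hepatitis only as a possibility and calls such effects transitory and manageable.

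Finally, the article condenses a fuller protocol whose table may be clearer. The kidney label reads "Kidneys (right and left) Rectum", which may come from text extraction; nothing is built on it. These points lower the weight of the concern. They do not explain why a mandatory table carries two kidney limits so far apart.

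**Conclusion.** The point holds in a limited form. The two kidney limits imply clearly different tolerances for any organ well below 606 cc. Under the assumed volumes, the absolute one is 50% to 80% of both kidneys against 33%, or the whole of a single kidney or more. It is therefore redundant or mis-stated, and the row leaves open whether it applies per kidney or combined. The conclusion rests on the assumed organ volumes, but it would change only if they were far larger.

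For the liver, the finding is a request to check: an outlying absolute figure with no companion limit, whose two possible readings differ on either side of 1,400 cc, and no demonstrated error.

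The point concerns treatment planning, eligibility and consistency between centres. It changes no sample size, error rate or analysis.

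**What to change.** Reconcile the two kidney limits with each other, with the full protocol and with the source that Table 3 cites. State whether they apply to each kidney or to both together. For the 200 cc and 700 cc entries, state whether each is the largest volume that may receive the dose or the smallest volume to be kept below it. Send the clarified table to all centres before further planning. Which limit is right is for the sponsor's radiation oncologists; none is proposed here.

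The cost is a table check, a notice to sites and possibly a re-check of existing plans with dose to the kidneys or liver. If an entry changes, the number of irradiable lesions, and with it eligibility under criterion 12, could move in either direction.
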